## 6 PARTICIPANT SELECTION

Participants will be recruited within 4 days of admission to a hospital ward at St Thomas's Hospital with hip fracture. In 2022, 255 patients were admitted to a hospital ward at St Thomas's Hospital with hip fracture. Previous trials of patients with hip fracture reported recruitment rates of 32% (of eligible and invited) in hospital.

The recruitment target aims to have sufficient participants to provide the operational experience to plan a definitive trial; provide reasonably robust estimates of our feasibility outcomes; and to estimate the variability of the proposed patient outcomes to inform a future sample size calculation. A recruitment target of 60 participants (30 per treatment arm) will allow overall retention rate at 12-weeks to be estimated with precision of  $\pm 11\%$ , using an exact 95% confidence interval, from previously observed retention rates of  $\sim 80\%$  for the same population. Assuming a non-differential retention rate of 80% at 12-week follow-up, this target will provide follow-up outcome data on  $\sim 24$  participants per arm.

### 6.1 Participant inclusion criteria

We will include adults

- aged 60 years or more.
- admitted to hospital for surgical repair of a low energy hip fracture.
- who are willing and able to provide consent or assent depending on the level of cognitive impairment.

We sought to employ as inclusive eligibility criteria as possible to maximize representativeness of the population (and to ensure that the intervention is assessed for patients in all three risk subgroups). This decision followed our PPI consultations and findings from our systematic review detailing inequities in access to trials of rehabilitation after hip fracture surgery (27.3% of potential participants of 35 trials were excluded based on factors that stratify healthcare opportunities and outcomes).

### 6.2 Participant exclusion criteria

We will exclude adults

- less than 60 years, to align with the National Hip Fracture Databases definition of the target population.
- not surgically treated, as this treatment approach is reserved for around 2% of patients in the UK who are often at the end of life.
- who broke their hip in hospital following admission for a different illness/injury as their anticipated care pathway and outcomes will vary from those who are admitted for hip fracture.
- who broke their hip following a high energy trauma e.g. road traffic accident.
- participating in other treatment trials and without agreement of both trial teams.

## **7 STUDY PROCEDURES**

### **7.1 Timeline**

The timeline for the trial is outlined in Table 1.

### **7.2 Screening Procedures**

An anonymous screening log will document the number of adults admitted with hip fracture, the number screened (the number ineligible and reasons for ineligibility, and reasons for eligible but not screened), the number ineligible after subgroup assignment (we will target enrolment of 20 participants to each subgroup), the number approached, and the number who declined (and why). For those eligible but declined, we will also retain data on their subgroup assignment to determine whether the rates of decline vary by subgroup. The screening log will be completed by the clinical team who would routinely treat/access this cohort of patients to ensure the common law duty of confidentiality will be upheld. A site principal investigator (PI) who would routinely treat/access this cohort of patients will be responsible for ensuring the accuracy of the log.

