A stratified approach to rehabilitation after hip fracture was subsequently developed. First, we developed and validated a subgrouping tool 'the stratify hip algorithm' (based on three multivariable prediction models) to identify patients at low-, intermediate- and high-risk of death and/or change in residence (to a higher level of care) using records for over 170,000 patients admitted to one of 173 hospitals in England and Wales. The approach requires entry of 5 pieces of information to a website: <https://stratifyhip.co.uk/> (age, sex, prefracture mobility, prefracture residence, and dementia diagnosis) to subgroup each patient. Overall, 31% of patients were assigned low-risk, 28% medium-risk, and 41% high-risk across three outcomes (in-hospital death, change in residence, 30-day death). Patients in the overall low-risk subgroup were typically less than 80 years old with the majority female (66%), admitted from home (91%), with outdoor mobility pre-fracture (83%), and no dementia diagnosis (95%). Compared to the overall low-risk subgroup, a greater proportion of patients in the overall medium-risk subgroup were older (94% aged 80 years or more), female (99%), and had a dementia diagnosis (14%). Compared to the overall medium-risk subgroup, patients in the high-risk subgroup were of a similar age (94% aged 80 years or more); however, a greater proportion was male (37%), with indoor/no mobility (69%), admitted from nursing/residential care (40%) with a dementia diagnosis (50%).

Next matched interventions were designed for each subgroup identified by the algorithm. These interventions were informed by qualitative interviews with patients, physiotherapists, and the multidisciplinary team, an umbrella review of systematic reviews of older adults who underwent rehabilitation interventions in the acute setting, recent systematic (including Cochrane) reviews, international guidelines, consultation with our public and patient involvement group 'TROOP' (further detail of TROOP available at [www.ppitroop.co.uk](http://www.ppitroop.co.uk)), and an intervention development workshop and survey (following a nominal group technique) to prioritize intervention components with key stakeholders.

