## **7.6 Schedule of assessments for each visit**

Participants will undergo screening, baseline assessment, assessment at intervention end, and assessment at 12-weeks post-randomisation. Assessments at baseline and intervention end will be in-person, over the telephone, or via MS TEAMS (the mode will be documented). Assessments at 12-weeks post-randomisation will be completed over the telephone or via MS TEAMS.

Screening for eligibility: Confirmation planned surgical intervention for hip fracture and aged 60 years or more. Additional assessment prior to consent will include a member of the direct care team's determination of capacity, confirmation whether the potential participant is enrolled in any other study, and subgroup assignment (to ensure no more than 12 participants from one subgroup enrolled to each arm of the study).

Baseline: Following consent and prior to randomisation, a member of the research team will collect the following participant characteristics: age, sex, ethnicity, fracture type, surgery type, Abbreviated Mental Test, Mini Nutritional Assessment, hospital concerns about falls

assessment, pre-fracture residential status (home, residential home, nursing home), living status (lives alone, with independent spouse, with dependent spouse, with family, with other), prefracture mobility. They will also collect patient-reported outcome measures which satisfy the core outcome set for hip fracture trials:

- a) health-related quality of life (EuroQoL EQ-5D-5L)
- b) activities of daily living (Barthel Index; Nottingham Extended Activities of Daily Living)
- c) falls related self-efficacy (Short Falls Efficacy Scale-International)
- d) pain (Numeric Rating Scale)
- e) walking ability (New Mobility Score)

A bespoke resource use data collection form will also be collected. This form can be collected both prior to and/or after randomisation but will be completed prior to discharge (and intervention end).

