## **14 STATISTICAL CONSIDERATIONS**

### **14.1 *Sample size***

The sample size was determined in consultation with the trial statistician. The recruitment target of 60 participants aims to have sufficient participants to provide the operational experience to plan a definitive trial; provide reasonably robust estimates of our feasibility outcomes; and to estimate the variability of the proposed patient outcomes to inform a future sample size calculation. A recruitment target of 60 participants (30 per treatment arm) will allow overall retention rate at 12-weeks to be estimated with precision of  $\pm 11\%$ , using an exact 95% confidence interval, from previously observed retention rates of  $\sim 80\%$  for the same population. Assuming a non-differential retention rate of 80% at 12-week follow-up, this target will provide follow-up outcome data on  $\sim 24$  participants per arm.

This required sample size will be attainable in practice. In 2022, 255 patients were admitted to a hospital ward at St Thomas's Hospital with hip fracture. Previous trials of patients with hip fracture reported recruitment rates of 32% in hospital.

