## **14.3 Quantitative analysis**

A CONSORT flow diagram will display data specifying counts of screened, eligible, approached, randomised, and completed enabling estimation of eligibility, recruitment, consent and follow-up rates. Confidence intervals for recruitment and retention rates will be produced to inform assumptions for planning the definitive trial. Rates of screened, eligible, approach and recruited will also be estimated for carers of participants enrolled into the medium- or high-risk intervention arm. Completion rates will be estimated for outcome measures collected at each time-point. Baseline characteristics will be summarised by allocated arm (and by subgroup assignment) with descriptive statistics (measures of central tendency and dispersion) to enable assessment of baseline comparability of arms (a degree of imbalance is anticipated in this small feasibility study). Patient-reported outcomes and treatment fidelity will be summarised by allocated arm (and by subgroup assignment) at each follow-up, with descriptive statistics (measures of central tendency and dispersion). Between-arm differences, including in changes from baseline, will be reported for the patient-reported outcomes with corresponding measures of dispersion to enable an assessment of sensitivity to change to inform primary outcome selection for a definitive trial and a formal power calculation for this outcome for a definitive trial.

For patients who do not speak English, the count of pseudo-anonymised patient-reported outcome measures circulated and returned by post will be documented. The content of the patient-reported outcome measure will be described narratively ensuring participant anonymity is preserved (the language versions circulated will not be specified in reporting).

The quantitative analysis will be completed by a trial statistician using R (<https://www.r-project.org/>) (or other well validated statistical packages) after database lock at trial end. The TSDMC will monitor screening/eligibility, approach and randomisation rates and safety reporting. There are no additional interim analyses planned. Qualitative analysis

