### **Figure 2: Progression criteria**

|                          | GO                                                              | AMEND                                                             | STOP                                                            |
|--------------------------|-----------------------------------------------------------------|-------------------------------------------------------------------|-----------------------------------------------------------------|
| Recruitment       | ≥40% eligible                                                   | 21-39% eligible                                                   | ≤20% eligible                                                   |
| Recruitment       | ≥50% eligible recruited                                         | 31-49% eligible recruited                                         | ≤30% eligible recruited                                         |
| Randomisation     | ≥70% of those recruited randomised                              | 49-70% of those recruited randomised                              | ≤48% of those recruited randomised                              |
| Fidelity          | ≥80% sessions included all intervention components as described | 51-79% sessions included all intervention components as described | ≤50% sessions included all intervention components as described |
| Outcome, 12-weeks | ≥80% completeness of EQ5D at 12-week follow-up                  | 51-79% completeness of EQ5D at 12-week follow-up                  | ≤50% completeness of EQ5D at 12-week follow-up                  |

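### The subgroup enrolment limits differ between sections and their effect is not separated out: patients turned away by a full subgroup count as ineligible, and the progression rates are planned only as overall rates

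*Protocol*

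**What the plan says.** - Section 2 gives the risk mix in the algorithm's source records: "Overall, 31% of patients were assigned low-risk, 28% medium-risk, and 41% high-risk across three outcomes".
- Section 6.1 gives the aim of the eligibility criteria: "to maximize representativeness of the population (and to ensure that the intervention is assessed for patients in all three risk subgroups").
- Section 7.2 lists among the screening log's counts "the number ineligible after subgroup assignment (we will target enrolment of 20 participants to each subgroup"). It also keeps the subgroup of eligible patients who decline, to see whether decline varies by subgroup.
- Section 7.6 applies subgroup assignment before consent "to ensure no more than 12 participants from one subgroup enrolled to each arm of the study".
- Section 14.1 sets the total: "A recruitment target of 60 participants (30 per treatment arm"). It plans one overall 12-week retention rate with a precision of ±11%, assuming 80%.
- Section 14.3: "Confidence intervals for recruitment and retention rates will be produced to inform assumptions for planning the definitive trial". Baseline data, patient-reported outcomes and fidelity are to be summarised by subgroup. No subgroup breakdown is named for recruitment, retention or completion rates.
- Figure 2 scores eligibility (GO from 40%, AMEND 21–39%) and completeness (GO at "≥80% completeness of EQ5D at 12-week follow-up", AMEND 51–79%), each as one rate with no subgroup rule.

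**The concern.** There are two separate problems.

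First, being turned away because a subgroup is full is a result of the design, not of a patient's suitability. Section 7.2 nevertheless calls it ineligibility, and Figure 2 uses the eligibility rate to decide on progression. The same site, with the same patients and staff, would record a lower rate the more tightly the limit is applied. A definitive trial without such limits would then be planned on too low a rate.

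Second, the limits set the enrolled risk mix. A pooled retention or completeness rate equals the rate in the source population only if the subgroups have the same rate or are enrolled in the population's proportions. The subgroups are defined by predicted death and change of residence, and section 2 describes half of the high-risk group as having a dementia diagnosis. Equal rates cannot be taken for granted. If the pooled rate lies close to 80%, the mix could help to decide between GO and AMEND.

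**Working it through.** **The plan's own figure.** For 48 of 60 (80%), the exact 95% interval is 67.7% to 89.2%, a half-width of 10.8 points, and 30 × 0.80 = 24 per arm. The stated ±11% and about 24 per arm are both right.

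**Permitted mixes.** Twelve per arm gives 2 × 12 = 24 per subgroup. With 60 in total, the smallest a subgroup can be is 60 − 48 = 12. The source mix applied to 60 gives 18.6/16.8/24.6. At 20/20/20 the high-risk share is 33.3%, which is 7.7 points below 41%. At 24/24/12 it is 20%, which is 21 points below.

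**Patients turned away.** Assume steady arrivals at 31/28/41 and equal uptake, and count patients who would consent.
- *Strict limit of 20.* The medium subgroup fills last, after 20/0.28 = 71.4 such patients. Of these, 71.4 − 60 = 11.4 are turned away, and 11.4/71.4 = 16%.
- *Limit of 24.* The high-risk subgroup fills after 24/0.41 = 58.5. The remaining 60 − 58.5 = 1.5 places come from the other 59% of arrivals and need 1.46/0.59 = 2.5 more. The total is 61.0, of whom 1.0 is turned away: about 2%. The expected mix is then about 19/17/24, close to the source mix.

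These are average-flow figures. Chance variation in the order of arrival would on average raise both.

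**Effect on Figure 2 eligibility.** The recorded rate is the clinical eligibility rate × (1 − share turned away). At an assumed clinical eligibility of 45%, a limit of 24 gives 45 × 0.98 = 44.1% (GO). A limit of 20 gives 45 × 0.84 = 37.8% (AMEND). Under the limit of 20, any clinical rate from 40% up to 40/0.84 = 47.6% would be recorded below 40%.

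**Effect of the mix on EQ-5D completeness.** Crude rate = Σ nₖrₖ/60. Standardised rate = 0.31 r_L + 0.28 r_M + 0.41 r_H. The subgroup rates are assumptions; the protocol gives none.

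| Assumed low/medium/high | Standardised | 20/20/20 | 24/24/12 | 12/24/24 |
|---|---|---|---|---|
| 80/80/80% | 80.0% | 80.0% | 80.0% | 80.0% |
| 85/80/75% | 79.5% | 80.0% | 81.0% | 79.0% |
| 90/85/65% | 78.35% | 80.0% | 83.0% | 78.0% |
| 95/90/55% | 77.2% | 80.0% | 85.0% | 77.0% |

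Crude minus standardised is 0, 0.5, 1.65 and 2.8 points at 20/20/20. It is 0, 1.5, 4.65 and 7.8 points at 24/24/12, and 0, −0.5, −0.35 and −0.2 points at 12/24/24. At 90/85/65% the chance of reaching 48 of 60 is 0.58 at 20/20/20, 0.80 at 24/24/12 and 0.42 at 12/24/24.

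**Cost in precision.** At 20/20/20 and 90/85/65%, the standard error is √(Σ nₖrₖ(1−rₖ))/60 = 5.0 points for the crude rate and √(Σ wₖ²rₖ(1−rₖ)/nₖ) = 5.3 points for the standardised rate.

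**The case against.** The best case for the plan runs as follows.
- *Sections 7.2 and 7.6 can be read as a target with a tolerance.* This is possible, but the protocol does not say at which number a subgroup closes, and the share turned away depends heavily on that number.
- *Subgroup limits are deliberate.* This stands. Section 6.1 wants the intervention assessed in all three subgroups, the primary objective is fidelity, and fidelity is already summarised by subgroup.
- *The raw material is already collected.* This also stands. The log counts exclusions after subgroup assignment as a separate item, decline is examined by subgroup, and randomisation is stratified by subgroup. What is missing is a rule that keeps subgroup closures out of the Figure 2 eligibility rate.
- *Crude or standardised is a matter for the analysis plan.* In part. The protocol states neither, so the crude reading is an inference. The enrolment limits, the use of ineligible for closures and the progression table are, however, fixed in the protocol.
- *Consultees may complete data for participants* (section 7.3.2), which could narrow the subgroup differences. This stands, and is one reason why the size is uncertain.

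A reader might infer that the GO or AMEND verdict depends on which subgroup filled, or that the overall rates will be too favourable. The documents do not support either as a general statement. If 20/20/20 is reached, every subgroup is full and the mix is fixed. The direction reverses slightly at 12/24/24. The 24/24/12 extreme needs far lower uptake among high-risk patients than among the others. A reader might also conclude that Figure 2 should be scored on a standardised rate. That is debatable, because the mix of a definitive trial depends on who consents, and 31/28/41 describes admissions.

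**Conclusion.** The point holds in a limited form. Sections 7.2 and 7.6 state different numbers without saying how they work together. Following the log as written lets subgroup closure lower a progression rate, by about 2% to 16% of otherwise eligible patients on average, if arrivals follow 31/28/41 and uptake is equal. That part needs no assumption about outcomes, and the upper end is enough to move a clinical eligibility rate in the 40s from GO to AMEND.

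The mix effect on retention and completeness is weaker. Over the assumed subgroup rates it is about 0 to 3 points at the planned mix, well inside the stated ±11%, and up to about 8 points only at 24/24/12 with a large gap between low and high risk. Near a threshold even a small shift can look decisive, but Figure 2's printed bands leave a gap between 79% and 80%, so a standardised value such as 79.5% is not clearly AMEND. The stated sample size and precision are not affected.

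**What to change.** 1. Reconcile sections 7.2 and 7.6: state whether 20 is a target or a limit, and at what number a subgroup closes.
2. In 14.3 and 14.4, exclude subgroup closures from the Figure 2 eligibility rate. Either count eligibility on the clinical criteria alone, or count it for each subgroup only while that subgroup is open. Report closures as their own line in the CONSORT diagram.
3. Report recruitment, retention and 12-week EQ-5D completeness by subgroup as well as overall.
4. Beside the crude rate, give the rate standardised to the screening-log mix (or to 31/28/41) as a sensitivity analysis for the progression decision, and say so before the data are seen.

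The cost is a few more lines of analysis on a variable already used to stratify randomisation, and a slightly wider interval for the standardised rate (standard error about 5.3 against 5.0 points in the example). Enrolment numbers and procedures need not change beyond settling the closing rule.

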### **7.3 Recruitment**

Participants will be recruited within 4 days of admission to a hospital ward at St Thomas's Hospital with hip fracture. This is to allow sufficient time to deliver the intervention, given the average length of stay after hip fracture is 16 days. Recruitment of this patient population within this timeframe has been completed successfully in previous UK trials. Patients may be recruited pre- or post- operatively. In the rare instance where a patient is recruited pre-operatively but then does not go on to have surgery, they will be removed from the trial and replaced.

A member of the direct care team will decide whether a potential participant has capacity to give informed consent.

#### **7.3.1 Participants with capacity**

Potential participants will first be approached by a member of the direct care team who will determine their interest in taking part in the trial and gain consent to share their contact details with a member of the research team. Consent to contact will be documented in the CRF and medical notes. A member of the research team will subsequently provide an explanation of the aims, methods, benefits and potential harms and a participation information leaflet. Potential participants will be given at least 24 hours to consider their participation in the study. A member of the research team will subsequently answer any questions prior to obtaining written informed consent to enter and be randomised into the trial. Non-English language speaking older adults will be supported to consider their enrolment in the trial with the use of language support at the Trust.

### **7.3.2 Participants without capacity**

For those who are considered as lacking capacity, agreement will be sought by a member of the research team from the patient and their consultee. If agreement is provided, the consultee will be provided with a consultee participant information leaflet and asked to sign a consultee declaration form. If the patient does not have a next of kin, the consultee may be a member of the patient's direct care team (who is not also a member of the research team). Subsequently, the member of the research team will seek assent from the patient for participation, as able. If a participant who lacks capacity indicates dissent, but their consultee advises involvement in the study, they will not be included in the study. This approach is in keeping with recommendations outlined by the Mental Capacity Act, 2005 and by the Alzheimer Europe Ethics of Dementia Research (<http://www.alzheimer-europe.org/Ethics/Ethical-issues-inpractice/Ethics-of-dementia-research/Informed-consent-to-dementia-research>).

Consultees will be invited to support the participant with data collection, or complete data collection on a participant's behalf. The number of consultees who declined to support data collection (and why) will be documented.

It is possible that a participant without capacity may see a capacity improvement during the study (e.g., for participants with pre/postoperative delirium that resolves). If this occurs, they will be informed of their enrolment in the study and what it involves, including the provision of the participant information leaflet and the opportunity to consent for themselves. They will be advised that they are free to withdraw from the trial at any point.

It is unlikely but possible a participant with capacity may see a capacity deterioration during the study. If this occurs, their original consent (with capacity) will be preserved. A consultee will be sought, provided a consultee participant information leaflet, and asked to sign a consultee declaration form. The consultee will be invited to support the participant with data collection, or complete data collection on a participant's behalf.

